## Abstract

**Background:**

Patients with persistent globus sensation, throat clearing, chronic cough, hoarseness, and other throat symptoms account for a large proportion of patients in ears, nose, and throat clinics. Laryngopharyngeal reflux disease (LPRD) is increasingly valued by otolaryngologists. Transcutaneous electrical acupoint stimulation (TEAS) is possibly a new method for the treatment of LPRD. This trial aims to determine whether TEAS combined with proton pump inhibitor (PPI) is better than PPI alone in the treatment of LPRD.

**Methods:**

This prospective randomized controlled trial will be implemented in a tertiary hospital in China. Seventy patients diagnosed with LPRD will be randomly assigned to the TEAS + PPI group (intervention group) or PPI group (control group), at a ratio of 1:1. In addition to using PPI, the intervention group will receive TEAS at four groups of acupoints, and each group will be treated for 15 min, once for 60 min, five times a week, for 12 weeks, 60 times. The main outcome will be changes in the Reflux Symptom Index scores at 4, 12, and 24 weeks after treatment. The secondary outcomes will include changes in the reflux finding score, Laryngopharyngeal Reflux-Health-related Quality of Life score, and throat pain visual analog scale score.

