### Outcomes

#### Primary outcome

The RSI is a widely used scale for diagnosing and evaluating LPRD. It is a well-established patient self-report questionnaire and is a tool with publicly available data. The RSI scale contains 9 items, which are scored on a 6-point Likert scale (0–5), with a score of 0–45. The higher the score, the more severe the symptoms. RSI > 13 points will be considered possible patients with LPR [29]. RSI remains the “standard” in this field, although it has some shortcomings and limitations [30]. Therefore, we will select it as the primary outcome to assess the severity of reflux. Participants will be evaluated for changes in scale scores before the start of the experiment (after the informed consent will be obtained) and at 4, 12, and 24 weeks of the experiment (Fig. 2). The last of the nine items of the RSI is a complex GORD problem that includes heartburn, chest pain, indigestion, and acid reflux. Patients with dyspepsia may reach 5 points on the ninth item, which may be mistaken for patients with LPR. Referring to the report of a clinical trial, we will require that after the ninth item is removed, the score must be greater than or equal to 10 to be included [31]. Significant improvement will be defined statistically here, when the total score values will decrease by more than 50%. In addition, the valid rate will be defined as the proportion of patients showing significant and effective improvements.

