### Dx-pH monitoring

The oropharyngeal pH test is an important test for the objective diagnosis of LPR. Some researchers compared the ability of oropharyngeal and esophageal pH monitoring to predict the response of patients with suspected LPR to PPI treatment, indicating that the oropharyngeal probe has a higher positive predictive power than esophageal measurement [36]. All patients will be required to undergo Dx-pH testing before enrollment to determine whether they have acid, alkaline, or mixed reflux. Only patients with acid reflux will be included. Because PPI has a great effect on acidic and mixed reflux, it can alkalize the gas and liquid of reflux and reduce the activity of pepsin, but it has little effect on alkaline reflux [37]. In previous studies, because of the time and economic cost of pH testing, most patients are unwilling to perform pH monitoring again after treatment. Therefore, we will consider pH detection as a secondary outcome.

All outcomes will be measured at the four time points of the study. Dx-pH monitoring will be performed at baseline and 12 weeks. LPR-HRQL score, throat pain VAS score, and RFS will be assessed at baseline, 4, and 12 weeks. RSI will be evaluated at baseline, and 4, 12, and 24 weeks. The time schedule for the inclusion of participants, intervention, and evaluation is shown in Fig. 3.

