### Statistical methods

#### Sample size

According to the previous literature on the use of PPI therapy in the Chinese population [38], after 3 months of LPRD treatment, the RSI score was approximately 11.7 points, and the standard deviation was approximately 6. We will estimate that the RSI score of the intervention group will be 4.5 points higher than that of the control group after treatment. Comparing two independent samples using a two-tailed *t*-test with an alpha value of 0.05% and 80% power, a sample size of 29 patients will be obtained. Considering a dropout rate of 10%, 33 patients will be recruited for each group. In actual recruitment, we will plan to recruit 35 participants for the intervention and control groups. We will plan to recruit sufficient participants by posting posters in ENT clinics for 4 months.

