#### Statistical analyses

The measurement data that conform to the normal distribution will be represented by the mean ± standard deviation, and the measurement data that do not conform to the normal distribution will be represented by M (P25, P75). The analysis will be performed based on intention-to-treat and will be performed using SPSS version 23.0. A bilateral *P* value of less than 0.05 will be considered significant. Continuous variables will be compared using the t-test or Mann–Whitney *U* test. The chi-squared test or Fisher’s exact test will be used to compare the qualitative data.

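### RSI change at weeks 4, 12 and 24 is jointly the primary outcome, with no deciding time point or multiplicity rule, while the sample size covers one comparison at 3 months

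*Protocol article*

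**What the plan says.** - **Abstract, Methods:** "The main outcome will be changes in the Reflux Symptom Index scores at 4, 12, and 24 weeks after treatment".
- **Outcomes, Primary outcome:** RSI is the primary outcome, with changes assessed before the start and "at 4, 12, and 24 weeks of the experiment". The same section adds a responder measure (a fall of more than 50% in total score) and a valid rate.
- **Dx-pH monitoring (closing schedule paragraph):** "RSI will be evaluated at baseline, and 4, 12, and 24 weeks".
- **Statistical analyses:** "Continuous variables will be compared using the t-test or Mann–Whitney" U test, and a two-sided P "value of less than 0.05 will be considered significant". No repeated-measures model, global test, hierarchy or alpha adjustment is mentioned.
- **Sample size:** one two-tailed two-sample t-test, based on a report that "after 3 months of LPRD treatment, the RSI score was approximately 11.7 points" with SD about 6. The difference is 4.5 points and power is 80%, giving 29 per group, 33 after 10% dropout, and 35 per group to be recruited.

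No section names one of the three visits as decisive or requires all three to be significant.

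**The concern.** The article does not leave the primary endpoint open for a later document to complete. It states three times as the main outcome, and a sample size that fits only one of them. A reader cannot tell which result decides the trial. If week 4 is significant and week 12 is not, or the reverse, the plan gives no agreed interpretation.

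This matters more than usual here. RSI is self-reported, and participants and outcome assessors know the allocation (Randomization and allocation concealment). With no deciding visit fixed in advance, the headline visit could be chosen after results are seen. The stated 0.05 would then no longer be the error rate of the primary claim.

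**Working it through.** **1. Reproduce the plan's sample size.** Inputs from Sample size: difference 4.5, SD 6, power 80%. Two-sided alpha is 0.05, as in Statistical analyses.

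- Normal approximation: n = 2 × (6/4.5)² × (1.960 + 0.842)² = 27.9 per group.
- Noncentral t: 28.9, so 29 per group, as stated.
- Dropout: 29/0.9 = 32.2, so 33, as stated.

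The Sample size section prints alpha as 0.05%. Taken literally (0.0005), that would need about 70 per group, so the 29 was computed at 0.05. That slip is a separate matter. What counts here is that 29 is the size for **one** test at 5%, using a 3-month value.

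**2. False positive rate if any one of three tests counts.** Under no effect, with standardised test statistics Z₁, Z₂, Z₃:

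rate = 1 − P(|Z₁| < 1.96, |Z₂| < 1.96, |Z₃| < 1.96)

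For independent tests this is 1 − 0.95³ = 14.3%. For equally correlated tests it is a trivariate normal probability. The article gives no between-visit correlation, so the correlation is an assumption and is shown as a range:

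| Assumed correlation | Rate |
|---|---|
| 0 (independent) | 14.3% |
| 0.3 | 13.6% |
| 0.5 | 12.5% |
| 0.7 | 10.9% |
| 0.8 | 9.8% |
| 0.9 | 8.4% |

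Simulated t-tests with 35 per group agree: 13.6% at 0.3, 12.7% at 0.5, 11.0% at 0.7.

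A correlation of 0.5 has some rationale for change scores. Suppose all visits, including baseline, have variance σ² and common correlation ρ. Two changes from the same baseline then have covariance σ²(1 − ρ) and variance 2σ²(1 − ρ) each, so their correlation is 0.5 whatever ρ is. Nothing in the article supports or rejects that equal-correlation structure.

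**3. Does any three-visit rule fit the planned size?** Assume the same 4.5-point difference and SD 6 at every visit.

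- *Any of three, Bonferroni:* alpha = 0.05/3 = 0.0167 per test. The noncentral t calculation gives 38.7, so 39 evaluable per group. With 10% dropout, 39/0.9 = 43.3, so 44 recruited. The planned 35 gives about 75% power per test if all are evaluable, and about 70% with 35 × 0.9 = 31.5 evaluable.
- *All three required:* no alpha adjustment is needed. With 29 evaluable per group each test has 80.1% power, so the chance that all three are significant cannot exceed 80.1%, and it is lower whenever the visits are less than perfectly correlated.
- *One named visit:* error is 5%, 29 per group stands, and power is 87% if all 35 are evaluable.

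Only the last rule matches the sample size as calculated.

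**The case against.** The strongest reply is that the any-of-three rule is read into silence. The article names the type of test and the threshold. It does not say that each visit yields its own primary decision, or that one significant visit is enough. A statistical analysis plan, not shown, could hold a combining rule, and the 3-month basis of the sample size already points to week 12. This stands as a limit on the size of the problem: the inflated rate must be stated conditionally. It does not remove the defect, because the article itself defines the main outcome at three times and sizes the trial for one.

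Three stronger readings are tempting but unsupported:

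- **A single rate of about 12%.** This needs a correlation near 0.58, which the article does not give. Only a range can be defended.
- **A still higher rate from responder tests at every visit.** The responder measure and the valid rate ("the valid rate will be defined as the proportion of patients showing significant and effective improvements") sit under Primary outcome, but nothing says they are tested at each visit or that a win there is a primary result. That the word effective is not defined is missing detail, which an article may leave to the full protocol.
- **A 12-week conflict in the clock,** between after treatment in the abstract and "at 4, 12, and 24 weeks of the experiment" in the body. The Secondary outcomes section places RFS at 4 and 12 weeks after treatment, and the schedule paragraph gives the same visits as baseline, 4 and 12 weeks. So after treatment most naturally means after treatment starts. This is loose wording.

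**Conclusion.** The point holds in conditional form. The article sets three co-listed primary times, a flat two-sided 0.05 and no decision rule, against a sample size for one comparison. If any one time counts, the false positive rate exceeds 5% for every correlation below 1, and is about 8% to 14% for assumed correlations from 0.9 down to 0. Protecting all three times by Bonferroni needs 39 evaluable per group against 35 planned, assuming the 4.5-point effect and SD 6 at each visit. The article does not show that the sponsor intends to claim success on any single visit; it only fails to rule this out. Week 12 as the intended time is inferred from the 3-month value and needs the sponsor's confirmation.

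**What to change.** Name RSI change from baseline at week 12 as the single primary endpoint, tested at two-sided 0.05. The sponsor should confirm that this is the 3-month time behind the sample size. Make weeks 4 and 24 and the proportion with a fall of more than 50% secondary.

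The trial is open-label, and Trial status gives June 1, 2021 as the date of first recruitment. The change should therefore be a dated amendment with a registry update, stating that it was made without reference to accrued outcome data. The quality assurance section already provides for updating the registry.

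At the same time, align the after-treatment wording in the abstract and in Secondary outcomes with the baseline-based schedule. Also note that the SD of 6 is for the 3-month score. If baseline and week 12 have equal SD and correlation ρ, the SD of change is 6 × √(2(1 − ρ)), which equals 6 at ρ = 0.5. The sponsor should state what is assumed.

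Cost: an amendment and a registry entry, with no extra visits. The 29 per group (33 with dropout) stands if the SD of change is about 6. The downside is that weeks 4 and 24 lose primary status. A fixed testing order or an adjusted alpha would also control the error rate, but Bonferroni would require more patients than planned.

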**Discussion:**

This trial will explore the feasibility of TEAS combined with PPI for the treatment of LPRD and provide potential evidence for its effectiveness and safety. The results of this study will be published in a peer-reviewed journal.

**Trial registration:**

Chinese Clinical Trial Registry ChiCTR2100046755. Registered on May 28, 2021.

**Supplementary Information:**

The online version contains supplementary material available at 10.1186/s13063-022-06193-0.

## Background

According to the 2002 statement of the American Academy of Otorhinolaryngology Head and Neck Surgery, laryngopharyngeal reflux (LPR) refers to the backflow of stomach contents into the laryngopharynx [1]. A recent review provided a more complete definition [2], which is defined as a type of upper aerodigestive tract inflammation related to the direct or indirect effects of gastroduodenal reflux, which may cause morphological changes. This definition considers that LPR stimulation caused by pepsin, bile salts, and other gastroduodenal proteins not only involves the mucosa of the laryngopharynx but also should include all mucosa of the upper gastrointestinal and respiratory tracts. Laryngopharyngeal reflux disease (LPRD) refers to a series of symptoms and signs experienced in the throat, middle ear, nasal cavity, trachea, and lung caused by LPR. There are two possible pathophysiological mechanisms of LPR: throat injury can be caused by direct contact and stimulation of reflux contents [3]. The other is that gastroduodenal contents can also stimulate the distal esophagus, stimulate chemoreceptors, and cause reflex cough, obstruction, and hypersecretion of the laryngopharyngeal mucosa [4–6]. The accumulation of viscous mucus can cause throat discomfort, such as postnasal drip, globus sensation, throat clearing, and coughing.

Xiao and Chen et al. reported that based on the Reflux Symptom Index (RSI) assessment, the prevalence of LPRD in China is approximately 10.15–18.8% [7, 8]. Similarly, two experts estimate that 5% of Greeks and 30% of British people experience LPR [9, 10]. Moreover, approximately half of patients with laryngeal and voice disorders have reflux factors [11]. Altman et al.’s study showed that between 1990 and 2001, the number of patients attending ears, nose, and throat (ENT) clinics due to LPR increased by 500% [12].

A study in the USA found that the cost of treating extraesophageal reflux symptoms in 281 patients was more than five times the estimated cost of treating patients with traditional gastroesophageal reflux disease (GORD) symptoms and that more than 50% of these costs were attributable to the use of proton pump inhibitors (PPIs). Therefore, LPR not only causes patient discomfort but also places a heavy economic burden on the US medical system [13].

PPI has become the first choice for the treatment of LPRD, although there is no particularly solid data support. Two recent meta-analyses based on randomized controlled trials have shown that PPI drugs have either no significant benefit or only a slight advantage over placebo [14, 15]. PPI treatment of LPR can only reduce the acidic components in the reflux but cannot completely prevent it; moreover, other more destructive reflux components, such as pepsin and bile acid, can survive even without strong acids. Therefore, it is of great significance to explore more effective treatments for LPRD.

Acupuncture is a common method of traditional Chinese medicine treatment. Studies have shown that acupuncture is used for the treatment of LPRD and has achieved good results. Transcutaneous electrical acupoint stimulation (TEAS) is a noninvasive, safe, and comfortable treatment that combines transcutaneous electrical nerve stimulation and acupoint stimulation. It is clinically used to replace electric and manual acupuncture [16]. TEAS has been used for perioperative anesthesia management and as part of postoperative recovery, which is useful for reducing intraoperative anesthesia medication [17], postoperative pain [18], postoperative nausea and vomiting [19], and postoperative recovery [20], and may be a promising treatment option for male infertility [21]. Currently, there has been no study on TEAS combined with PPI in the treatment of LPRD; thus, this trial has strong innovation and practical significance. This trial aims to evaluate the effectiveness and safety of this new treatment method for LPRD.

## Methods/design

### Study design

This prospective, randomized, parallel-designed clinical trial will be conducted in a tertiary hospital in Anhui, China. The trial protocol has been approved and reviewed by the Clinical Medical Research Ethics Committee of the First Affiliated Hospital of Anhui Medical University (PJ2021-04-20) and will be reported in accordance with the SPIRIT guidelines [22]. The corresponding author will be responsible for scientific supervision of the experiment. The study was registered with the Chinese Clinical Trial Registration Center (ChiCTR2100046755) on May 28, 2021.

### Study population

The study population will include patients diagnosed with LPRD in the Outpatient Department of Otorhinolaryngology Head and Neck Surgery of the First Affiliated Hospital of Anhui Medical University, People’s Republic of China. Two members of our research team will be responsible for recruiting potential trial participants. Written informed consent will be obtained by the clinical research coordinator at the outpatient department before randomization.

### Inclusion criteria

 ① Patients aged ≥ 18 years

② Patients with symptoms of globus sensation, continuous throat clearing, hoarseness, pronunciation fatigue, throat pain, chronic cough, and dyspnea for more than 6 weeks

③ Patients with RSI > 13 points and/or RFS > 7 points, with Dx-pH monitoring diagnosed as acid reflux

④ Patients who agree to sign an informed consent form and participate in clinical trials

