### Exclusion criteria

 ① Patients with pharyngeal discomfort caused by bacterial or viral pharyngitis

② Patient with erosive gastroesophageal reflux, laryngeal cancer, esophageal cancer, gastric cancer, and other diseases revealed by upper gastrointestinal endoscopy or laryngoscopy

③ Patients with a history of esophageal or stomach surgery and neck radiotherapy

④ Patients with severe liver, kidney, and other organ dysfunctions and are unable to tolerate medications or allergic to medications

⑤ Patients receiving proton pump inhibitor therapy or other research drugs in the previous month

⑥ Patients who are pregnant or breastfeeding

⑦ Patients with RSI scale score (excluding the ninth item) < 10 points

⑧ Patients taking clopidogrel or warfarin

⑨ Patients contraindicated to undergo TEAS because of the following: skin rash or local infection or implantation of a pacemaker or defibrillator, electrode pads causing skin allergies or itching, acute diseases, infectious diseases, malignant tumors, cardiovascular and cerebrovascular diseases, and other malignant diseases

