#### Secondary outcomes

The reflux finding score (RFS) is a widely used scale [32]. According to the results of laryngoscopy, it assesses whether there are signs of vocal cord edema, granuloma in the larynx, posterior hyperplasia, mucosal hyperemia, or erythema. The total RFS score ranges from 0 to 29. Patients will be instructed to undergo laryngoscopy before treatment and 4 and 12 weeks after treatment to objectively assess the changes in reflux signs.

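### Entry sets no floor on RFS, yet RFS change is compared without adjusting for baseline RFS, which gives up precision on the laryngoscopic secondary outcome

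*Protocol article*

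**What the plan says.** Under Inclusion criteria, the third criterion reads "Patients with RSI > 13 points and/or RFS > 7 points, with Dx-pH monitoring diagnosed as acid reflux". The two scores are alternatives, so RSI above 13 together with acid reflux on Dx-pH monitoring is enough, whatever the RFS.

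The seventh item under Exclusion criteria puts a second floor on symptoms by excluding "Patients with RSI scale score (excluding the ninth item) < 10 points". RFS has no matching floor. Its scale is given under Secondary outcomes: "The total RFS score ranges from 0 to 29".

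RFS is also an outcome. The abstract says "The secondary outcomes will include changes in the reflux finding score". Under Secondary outcomes, "Patients will be instructed to undergo laryngoscopy before treatment and 4 and 12 weeks after treatment to objectively assess the changes in reflux signs". The timing is repeated under Dx-pH monitoring: "LPR-HRQL score, throat pain VAS score, and RFS will be assessed at baseline, 4, and 12 weeks". Baseline RFS is thus planned for every patient.

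Statistical analyses gives one rule for all continuous outcomes: "Continuous variables will be compared using the t-test or Mann–Whitney" U test, with "The analysis will be performed based on intention-to-treat". It names no baseline covariate. The document gives no RFS standard deviation, no expected RFS effect, no baseline RFS distribution and no expected share with RFS of 7 or less.

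**The concern.** Two choices work against each other. Entry leaves baseline RFS free to range from 0 upwards, so patients may start at very different levels. The analysis then does not use baseline RFS as a covariate, although it is the measurement most likely to explain a patient's later RFS.

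A second issue comes from the scale. RFS cannot fall below 0, so a patient who enters at 7 or less can lose at most 7 points, and a patient who enters at 0 can lose none. If such patients are many and show a smaller effect, the average difference between arms shrinks.

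What is at stake is the precision and readability of the laryngoscopic result. RFS and Dx-pH monitoring are the outcomes that are not self-reported, and the protocol itself notes that most patients in earlier studies were unwilling to repeat pH testing. RFS may therefore be the more complete of the two, although its assessors also know the allocation.

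**Working it through.** **1. The plan's own figure.** The only sample size is for RSI. With a difference of 4.5 and SD 6, d = 4.5/6 = 0.75. A two-sample t-test at two-sided 0.05 (the level in Statistical analyses) and 80% power needs 28.9, so 29 per arm. With 10% dropout, 29/0.9 = 32.2, so 33. Both stated figures reproduce. RFS plays no part in them, and there is no RFS figure to reproduce.

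**2. What adjustment gains.** Assume equal SD σ at baseline and follow-up, and correlation ρ between them. Per-patient variances are:

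- final score: σ²
- change score: 2(1 − ρ)σ²
- linear model with baseline: (1 − ρ²)σ²

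The ratio to the change score is (1 − ρ²)/[2(1 − ρ)] = (1 + ρ)/2. The ratio to the final score is 1 − ρ².

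| ρ (assumed) | Adjusted vs change score | Adjusted vs final score |
|---|---|---|
| 0.5 | 75% | 75% |
| 0.7 | 85% | 51% |
| 0.8 | 90% | 36% |

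Interval width goes with the square root. Against the change score, the interval is about 13% narrower at ρ = 0.5 (√0.75 = 0.87) and about 5% narrower at ρ = 0.8 (√0.90 = 0.95).

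**3. What dilution could do, on assumptions only.** Let q be the share entering with RFS of 7 or less, and f the fraction of the full effect that they show. The average effect is d × [(1 − q) + q × f]. Take 31 per arm (35 less 10%, rounded down) and d = 0.723, chosen so that power is 80% when q = 0. The SD is held fixed. Power of the two-sided 0.05 t-test:

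| q | All patients, f = 1 | All patients, f = 0.5 | All patients, f = 0 | Only RFS > 7, 31 × (1 − q) per arm |
|---|---|---|---|---|
| 20% | 80% | 71% | 61% | 70% |
| 35% | 80% | 64% | 44% | 61% |
| 50% | 80% | 56% | 29% | 49% |

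The document gives neither q nor f. The table shows only that the loss may be anything from none to large.

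**4. Whether adjustment undoes dilution.** With ρ = 0.5 the standardised effect is divided by √0.75. At q = 0, power rises from 80% to 90%. At q = 20% it rises from 71% to 83% (f = 0.5) or from 61% to 74% (f = 0). The gain is already there when nobody enters with RFS of 7 or less, and the fall from 90% to 83% or 74% remains after adjustment. Adjustment therefore restores precision. It does not restore effect in patients near the floor.

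**The case against.** The strongest reply is that nothing here is wrong. Broad entry followed by an intention-to-treat comparison is coherent, and it estimates without bias the mean RFS effect in the patients enrolled. RFS is secondary and carries no power claim. All of that stands.

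It can also be said that baseline RFS is not ignored, because the outcome is described as a change and a change score uses baseline by subtraction. This stands too. It is why the gain is only 10% to 25% of variance against the change score, and why the larger saving against a final score applies only if final scores are what is compared. Subtraction gives baseline a fixed weight of one; the model estimates the weight.

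A further reply is that covariates belong in a separate analysis plan, which is not available here. That plan could add one. But Statistical analyses does name a method for all continuous outcomes, and a better one using data already planned is available, so the stated choice can be reviewed.

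A reader might infer more: that patients without reflux signs enter, and that they dilute the RFS comparison. The document does not support this. RFS above 7 is one of two alternative entry routes, and no normal value is defined. Scores of 1 to 7 still record signs that can improve. If these patients respond equally there is no dilution, and their number is unknown. Nor does the lack of adjustment cause any dilution. It would also go too far to say that a null RFS result could not be interpreted, since baseline RFS is recorded and can be examined.

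**Conclusion.** The point holds as a modest loss of precision on one secondary outcome. Entry sets no floor on RFS, and the stated test makes no covariate use of baseline RFS. Under an assumed correlation of 0.5 to 0.8 and equal SDs, adjustment would leave 75% to 90% of the change-score variance, or 75% to 36% of the final-score variance.

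Type I error, the validity of the intention-to-treat comparison, and the primary RSI sample size are unaffected. Dilution by patients with RFS of 7 or less is possible, but its size cannot be derived from the document. A comparison restricted to RFS above 7 is not a cure: when the other patients show half the effect, it has slightly to clearly less power than the comparison in all patients (70%, 61% and 49% against 71%, 64% and 56%). It gains power only if those patients show little effect.

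**What to change.** Leave eligibility as it is. In Statistical analyses, state that RFS at week 4 and at week 12 will be compared between arms, among all randomised patients, with a linear model that includes baseline RFS, and that the adjusted mean difference will be reported with its 95% CI. Taking the follow-up score or the change as the response gives the same adjusted difference, so the wording about change can stay.

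Report by arm the number of patients with baseline RFS of 7 or less. A comparison in patients with baseline RFS above 7 is optional; if included, prespecify it and label it supportive, so that it cannot replace the result in all patients.

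The cost is a sentence or two in the analysis section, settled before the data are analysed. It needs no extra patients, visits or measurements.
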